### Primary and secondary outcomes

In this study, participants’ QoL was the primary outcomes, whereas participants’ muscle strength, fatigue, hematological indicators, exercise adherence, and adverse events were the secondary outcomes. All outcomes were measured at the time of neutrophil and platelet engraftment (± 1 day, T0), discharge from the transplantation module (± 1 day, T1), discharge from the hospital (± 1 day, T2), and 100 days post-transplantation (± 5 days, T3). Evaluations of T0 will be administered by the [name] enrolling the patient as part of the baseline assessment. Follow-up evaluations will be administered by [name], who are blinded to the patient’s group allocation. All assessors will be trained by the rehabilitation therapist on the steering committee before the start of the trial, and periodic meetings between the evaluators will be established fortnightly to promote internal transparency and consolidate data collection procedures. T0, T1, and T2 measurements will be performed in the inpatient of hematology, and T3 measurements will be performed in the inpatient or outpatient clinic of hematology, depending on the patient’s follow-up results.

### Variables and measurement instruments

Sociodemographic and clinical variables: To characterize the samples, sociodemographic and clinical data were extracted from the participants, containing age, gender, marital status, educational level, professional/employment status, household income, duration of AA, medication, and type of treatment.QoL: it was measured using the validated European Organization for Research and Treatment of Cancer Quality of Life Questionnaire-Core 30 (EORTC QLQ-C30) [29]. This questionnaire consists of 30 items covering 15 domains, which reflect the patient’s physical, role, emotional, cognitive and social functioning, a global quality of life domain, together with fatigue, nausea and vomiting, pain, dyspnea, insomnia, loss of appetite, constipation, diarrhea, and financial difficulties. All items were rated on a 4-point response scale ranging from 1 (not at all) to 4 (very much) points, except for the two items measuring general health and QoL (summarized as global QoL) that were rated on a visual analogue scale from 1 ~ 7 points. All scales were transformed to a percentile scale from 0 ~ 100 points, with the higher scores representing better functioning and global QoL, whereas the higher scores on the symptom scales indicated the higher levels of symptoms or problems.Upper limb muscle strength: it was assessed by measuring the grip strength using a hand dynamometer (EH101, Camry, China) [30]. To be specific, the participant was asked to sit upright in a chair and place the feet on the floor. The shoulder of the limb to be tested was kept adducted and neutral for rotation, with the elbow being flexed at 90°, wrist extension between 0 and 30° and ulnar deviation of 0 ~ 15°. The left and right hands were alternately measured thrice each and the average value was taken as the grip strength of the participant. During the test, the participants were constantly verbally encouraged to use their maximum strength.Lower limb muscle strength: it was evaluated with the Five Times Sit to Stand Test (FTSST) [31]. In brief, participants were required to sit in an armless chair at a standard height (45 cm) and tested on the duration of 5 sit-to-stand movements. In the test procedure, the participants were asked to stand upright with their upper body, with arms crossing over the chest and feet flat on the floor. Participants were asked to stand up completely without using their upper limbs and then sit down again.Fatigue: it was measured with the Brief Fatigue Inventory (BFI) questionnaire [32]. The BFI questionnaire covers 10 items. The first item determines whether there has been abnormal fatigue over the last week using a “yes” or “no” option. The other items determine the current level of fatigue and the impacts of fatigue on general activity, mood, walking ability, relationships with others, and enjoyment of life. Each item is based on a 0–10-point scale, with a score of 0 representing the best state and no fatigue, whereas that of 10 indicating the worst state of fatigue. Participants were asked to mark their answers to each question based on their perceived level of fatigue, and the overall fatigue level was measured by calculating the total score of items 2 to 10 divided by 9. To be specific, a score of 0 meant no fatigue, while those of 0.1 ~ 3.9, 4 ~ 6.9, 7 ~ 9.9, and 10 were indicative of mild, moderate, severe, and very severe fatigue, separately.Hematological indicators: These indicators included platelet (PLT), neutrophil (Neu), hemoglobin (HB), and reticulocyte (Ret) counts in the peripheral blood of participants.Exercise adherence: it was assessed by the exercise attainment rate, which was the number of people attaining the standard/total number of people × 100%. Exercise attainment was defined as exercising at least thrice a week for 30 min or longer (or ≥ 10 min each time for a cumulative total of 30 min).Adverse events: the proportion of adverse events occurring during the study period was determined.

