Currently, meta-analyses have confirmed the positive impact of exercise interventions on the physical and psychosocial functioning and quality of life of transplant patients [15, 16]. However, as evidenced by the diversity of interventions and mixed hematologic and cancer populations, most of the existing studies have methodological limitations [17]. A mixed sample including both malignant and non-malignant hematology disorders that received HSCT was selected for most studies. No subgroup analysis was performed to determine whether it was the same hematologic disease. The symptoms and treatment modalities of patients with different hematologic diseases show significant differences. For example, malignant hematologic diseases (like leukemia) have a high risk of recurrence after transplantation, and disease recurrence is the leading cause of death after transplantation [18, 19]. By contrast, benign hematologic diseases such as AA have a lower risk of recurrence after transplantation, and the leading cause of death after transplantation refers to complications including graft-versus-host disease (GVHD) [20]. These differences in clinical characteristics support the need for exercise rehabilitation intervention studies in the HSCT-AA population. Meanwhile, we believe that studies on exercise interventions for malignant hematological diseases [21], lymphoma [22], and MDS [23] are also underway. To our knowledge, there is limited published literature on exercise rehabilitation in HSCT-AA patients. It provides an opportunity to examine the effectiveness of exercise interventions in benign but severe hematologic diseases such as HSCT-AA. The study hypotheses are as follows: (1) compared to the control group, exercise rehabilitation will result in a greater improvement on QoL (primary hypothesis); (2) compared to the control group, exercise rehabilitation will result in a greater improvement in muscle strength; (3) compared to the control group, exercise rehabilitation will result in greater improvement on fatigue and hematological indicators.

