### Intervention

The intervention group received a structured exercise rehabilitation program, which was mainly developed by our team through preliminary literature research and by inviting experts in the relevant fields (including hematologists, nurses, and rehabilitation therapists) [24]. The exercise rehabilitation was divided into 3 phases according to the different periods of the patient’s transplantation; each phase involved warm-up, formal, and finishing exercises, and was tailored according to the strength of each participant.Phase 1: Exercise rehabilitation in the transplantation module (neutrophil and platelet engraftment to out of the transplantation module). Considering that the patient was weak in the early post-transplantation period, exercises in this phase were mainly bed and bedside activities. The warm-up exercises were mainly lip reduction-abdominal breathing with progressive relaxation exercises (involving hand muscles, arm muscles, hip muscles, thigh muscles, calf muscles, and toe muscles), for exercising the muscles of the whole body; the aerobic exercises in formal exercises were mostly performed with bed-side bicycles; the resistance exercises were mainly bed or bedside elastic band exercises performed by the patient (involving biceps, triceps, psoas major, abdominal, gluteal and foot muscles); and the finishing exercises wrapped up with progressive relaxation exercises.Phase 2: Exercise rehabilitation in the hematology ward (during admission to the general ward).

Patients who were transferred from the transplant module were in better condition than before, so it was appropriate to increase the intensity of exercises and move from bed to floor. The warm-up exercise included 6 movements (including head exercise, shoulder circuit, chest expansion, waist circuit, knee circuit, and wrist and ankle exercises) to avoid injury during exercise; the aerobic exercise options for formal exercises included Baduan Jin and Tai Chi; the resistance exercise was a stretch band exercise consisting of 8 movements (more difficult than before); and the finishing exercise was a relaxing stretch of the whole body in 8 movements from head to toe.Phase 3: Out-of-hospital exercise rehabilitation (post-discharge to 100 days post-transplantation).

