## Statistical analysis

SPSS26.0 was adopted for statistical analysis of data. Missing data were filled in using the Last observation carried forward (LOCF) and statistical analysis was conducted following the intention-to-treat (ITT) principle. Statistical tests were carried out with two-sided tests and *P* 0.05 was considered a statistically significant difference. Gender, education level, marital status, exercise adherence, and incidence of adverse events were described as frequencies and percentages. In the meantime, age, duration of AA, time to HSCT and QoL, muscle strength, fatigue, PLT, Neu, HB, and Ret counts were described as means and standard deviations if they conformed to normal distribution, or median if they conformed to non-normal distribution. The chi-square test or *t-*test was employed to compare differences between the intervention and control groups. Taking into account the potential variations in age, gender, and education level, analysis of variance (ANOVA) was conducted to assess the development of outcomes over time. Additionally, repeated measures analysis was used to analyze scores at baseline and follow-up scores of all measures.

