### Limitations

Several limitations should be noted in this work. Firstly, HSCT-AA patients may be frail due to treatment and disease, and the patient attrition may be high after follow-up for 100 days post-transplantation. We will consider other measures to remind patients to participate in the follow-up study. Secondly, the control group was mainly provided with usual care together with exercise-related health education, which may have underestimated the intervention effect. Nevertheless, we consider that it would be unethical to include control subjects without any intervention. Finally, the white paper report mentions that HSCT patients should receive multimodal interventions, including exercise, nutrition, and return to work [34]. However, this study did not include a nutritional assessment or dietary intervention, which is considered another limitation of this exercise-focused intervention.

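### The Five Times Sit to Stand Test has no score for inability, and the blanket LOCF rule would replace such a failure with an earlier, better time

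*Protocol article*

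**What the plan says.** Under Variables and measurement instruments, the protocol article assesses lower-limb strength with the Five Times Sit to Stand Test (FTSST). Participants are "tested on the duration of 5 sit-to-stand movements", with arms crossed, and "Participants were asked to stand up completely without using their upper limbs and then sit down again". No value is given for a patient who cannot finish. The same section does set out scoring for the EORTC QLQ-C30 and the Brief Fatigue Inventory.

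Under Statistical analysis: "Missing data were filled in using the Last observation carried forward (LOCF"), with analysis by intention to treat. No outcome or reason for absence is exempted.

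The measure serves a stated hypothesis in Background: "compared to the control group, exercise rehabilitation will result in a greater improvement in muscle strength". It is secondary: under Primary and secondary outcomes, "muscle strength, fatigue, hematological indicators, exercise adherence, and adverse events were the secondary outcomes".

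On the patients' condition, the Intervention section says of Phase 1: "Considering that the patient was weak in the early post-transplantation period, exercises in this phase were mainly bed and bedside activities". Limitations adds that "HSCT-AA patients may be frail due to treatment and disease".

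On timing, Primary and secondary outcomes has every outcome measured at T0, T1, T2 and T3. Table 1 marks the FTSST only at t1, t2 and t3.

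**The concern.** A timed performance test has a natural worst result, which is not being able to do it. That result carries information: it marks the weakest patients. If the data hold only a blank, the one stated rule reaches back to the last visit at which the patient could stand. Any completed time is better than inability, so the filled value always errs in the patient's favour.

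FTSST is one of the two measures behind the muscle-strength hypothesis; grip strength is the other. If exercise preserves strength, one way this shows is that fewer exercisers than controls lose the ability to stand. LOCF would erase that part of the contrast. If instead more exercisers become unable, LOCF would hide it and flatter the intervention. Unless inability is recorded separately from a missed visit, nobody could later tell which had happened.

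**Working it through.** **The plan's own figure.** The article gives no expected mean, SD, effect or failure rate for FTSST. Its only sample-size figure is for QoL: n = 2 × (1.960 + 0.842)² × (17.6/12.3)² = 32.1, so 33 per group as stated. Then 33/(1 − 0.20) = 41.25, against the stated 41. This reproduces to within one patient and is not affected by the present point. Every FTSST input below is an assumption.

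**Step 1: direction.** Let pC and pE be the proportions unable at the final visit, mC and mE the mean times of completers, W the value that scores inability, and L the mean carried-forward time of those unable, taken as equal in both arms. The benefit (control minus exercise, in seconds) is

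- failures scored: (1 − pC)mC + pC·W − [(1 − pE)mE + pE·W]
- failures filled by LOCF: the same with L in place of W
- LOCF minus scored: −(pC − pE)(W − L)

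The sign depends only on pC − pE. With mC = 14, mE = 12, W = 30 and L = 15:

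| Unable, control / exercise | Scored | LOCF | LOCF − scored |
|---|---|---|---|
| 10% / 5% | 15.60 − 12.90 = 2.70 | 14.10 − 12.15 = 1.95 | −0.75 |
| 10% / 10% | 15.60 − 13.80 = 1.80 | 14.10 − 12.30 = 1.80 | 0 |
| 5% / 10% | 14.80 − 13.80 = 1.00 | 14.05 − 12.30 = 1.75 | +0.75 |

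**Step 2: size when failure follows from weakness.** Assume a latent time with T0 mean 14 s, SD 4 s, correlation 0.6 with the final visit, inability above 20 s, and a true benefit of 2.0 s. Patients are those testable at T0.

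| Control course | Unable, control / exercise | LOCF | Failures dropped | Failures set to 20 s |
|---|---|---|---|---|
| Worsens 4 s | 27% / 13% | 0.90 | 1.16 | 1.60 |
| Worsens 2 s | 13% / 5% | 1.49 | 1.46 | 1.82 |
| Stable | 5% / 1% | 1.82 | 1.73 | 1.94 |
| Recovers 3 s | 0.6% / 0.1% | 1.97 | 1.94 | 1.99 |

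With no true effect and 13% unable in each arm, every rule gives about 0.

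**Step 3: a second model.** Assume 41 per arm, log-normal times with log-SD 0.45, control medians 15 s at T0 and 14 s at T3, correlation 0.5, and a 22% reduction with exercise. The true mean difference is 14 × exp(0.45²/2) × 0.22 = 3.4 s. With inability above 30, 25 or 20 s, about 5%, 10% or 21% of controls (1%, 3% or 9% of exercisers) are unable at T3. LOCF then estimates about 2.8, 2.4 or 1.8 s. Power with LOCF and a t-test is about 64%, 59–62% and 52%, against 66–68% when inability is ranked worst. The same cut-offs imply 6%, 13% and 26% unable at T0, so the last case is extreme. Only T0 and T3 are modelled; with four visits LOCF would reach for T2 or T1 first.

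**Step 4: is there an earlier value to carry?** If the text is followed, a patient who first fails at T1 has a T0 time. If Table 1 is followed, that patient has none and LOCF cannot fill the gap. The two places lead to different data for the same patient.

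**The case against.** The strongest reply is that nothing in the article says a failed test is coded as missing. The FTSST description is expressly brief and cites a source, and scoring of an uncompleted test may sit in an assessment form, full protocol or analysis plan that is not shown. This stands as a limit: missing is the default reading, not a stated one. It does not remove the point, because the article fixes a rule for absent values without exception and offers no other code for inability.

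A reader might infer that the FTSST effect is simply biased toward zero. The documents do not support that. It requires more failures in control; Step 1 shows no shift with equal rates and an overstated benefit if exercisers fail more.

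A reader might also infer that LOCF drops patients, or that inability at T0 biases the comparison. LOCF leaves a gap only where no earlier time exists. Under Randomization and blinding, participants learn their allocation after the baseline assessments, so T0 failures are not caused by the intervention; losing them costs mainly precision and generalisability.

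Finally, failures may be rare when it matters. The weakness described belongs to the early phase, the Intervention section describes patients as improving once they leave the transplant module, the frailty remark is offered as a reason for attrition, and severe skeletal muscle, heart and lung changes are excluded at entry. This is fair, and it is why the size is left open. Those exclusions do not, however, cover weakness that develops after transplantation.

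**Conclusion.** The point holds in conditional form. FTSST gives no time for a patient who cannot complete it, no score for inability is stated, and LOCF as written would treat an informative failure as maintained strength. The direction depends on which arm fails more; toward zero is what the trial's own hypothesis implies, but it is not certain.

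The size cannot be fixed from the documents. Under the assumptions above it is negligible below about 1% failures (1.97 of 2.0 s) and material at around 10% or more in control (1.49 of 2.0 s at 13% versus 5%; about 2.4 of 3.4 s at 10% versus 3%). These figures rest on assumed times, correlations and cut-offs, and on failed tests being coded as missing. The reach is one of two strength measures within a secondary outcome; grip strength, the primary QoL outcome and the sample size are untouched. The change is worth making because it is cheap and because unrecorded failures may not be recoverable later.

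**What to change.** 1. On the assessment form, record 'unable to complete' as an FTSST result at every visit, distinct from a visit that did not take place.
2. In the analysis section, exempt that result from LOCF. Give it the worst rank, tied and below the slowest completed time, and compare the arms with a rank-based test; a prespecified ceiling time is an acceptable alternative. Keep the general missing-data method for missed visits only. Replacing LOCF with a missing-at-random model would not be enough, because the absent value is itself the poor outcome.
3. Report the number and proportion unable by arm and visit.
4. Reconcile Primary and secondary outcomes with Table 1 on whether FTSST is measured at T0.

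The cost is about one line on the form, one in the analysis section and a correction to the text or the table. The small downside is that a rank comparison gives no mean difference in seconds; the proportion unable and the times among completers can be reported beside it as description.

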
### Participant timeline

The participant timeline is shown in Table 1.

**Table 1 Tab1:** Participant timeline

	STUDY PERIOD			
	Baseline	Post-allocation		
TIMEPOINT^a^	*t*_*0*_	*t*_*1*_	*t*_*2*_	*t*_*3*_
ENROLMENT:				
Eligibility screen	X			
Informed consent	X			
*Demographics*	X			
*Medical history*	X			
INTERVENTION:				
*[Intervention group]*		X	X	X
*[Control group]*		X	X	X
ASSESSMENTS:				
*[EORTC QLQ-C30]*		X	X	X
*[hand dynamometer]*		X	X	X
*[ FTSST]*		X	X	X
*[BFI]*		X	X	X
*[Number and volume of RBC and PLT transfusions]*				X
*[Hematological indicators]*		X	X	X
*[Recruitment rate]*				X
*[Drop-out rate]*				X
*[Exercise adherence]*		X	X	X
* [Adverse events]*				X

^a^***t***_***0***_: the neutrophil and platelet engraftment (± 1day); ***t***_***1***_: discharge from the transplantation module (± 1 day); ***t***_***2***_: hospital discharge (± 1 day); ***t***_***3***_: 100 days post-transplantation (± 5 days)

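### Hypothesis 3 is tested on measured hemoglobin and platelet counts, which transfusion can pull together between arms, while the transfusion data listed in Table 1 have no role in the outcomes or analysis

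*Protocol article*

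**What the plan says.** The third hypothesis in the Background is that "exercise rehabilitation will result in greater improvement on fatigue and hematological indicators". The section Primary and secondary outcomes places the indicators among the secondary outcomes: "muscle strength, fatigue, hematological indicators, exercise adherence, and adverse events were the secondary outcomes". Transfusion is not on that list.

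Variables and measurement instruments defines the indicators: "These indicators included platelet (PLT), neutrophil (Neu), hemoglobin (HB), and reticulocyte (Ret) counts in the peripheral blood of participants". It gives no rule for a value measured soon after a transfusion.

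Table 1 (Participant timeline) has a row for "Number and volume of RBC and PLT transfusions", marked once, at t3.

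Statistical analysis summarises the counts: "fatigue, PLT, Neu, HB, and Ret counts were described as means and standard deviations if they conformed to normal distribution". Otherwise the median is reported. For group comparison it names the chi-square test or t-test, which "was employed to compare differences between the intervention and control groups". It continues: "Taking into account the potential variations in age, gender, and education level, analysis of variance (ANOVA) was conducted". It also applies a repeated measures analysis to the baseline and follow-up scores of all measures. Transfusion appears in none of these steps.

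**The concern.** HB and PLT are meant to show whether recovery is better with exercise. Both can be raised from outside: a patient whose own value is low may be transfused, and the next measured value is then higher than recovery alone would give. If one arm recovers less well, more of its patients are topped up, and the measured means move closer together. The raw comparison then describes recovery plus transfusion support, whereas the hypothesis concerns recovery.

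The protocol's own content suggests this can happen during follow-up. Table 1 plans to count red-cell and platelet transfusions, and the Intervention section sets resistance-exercise bands for platelet counts below 20, 20 to 30 and 30 to 50 × 10^9/L.

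At stake is the reading of two of the four components of one secondary outcome. A null result for HB or PLT could mean no benefit, or a benefit partly hidden by transfusion. The data that would help to tell these apart are listed for collection and then left without a use.

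**Working it through.** **1. The plan's own figure.** The only calculation in the document is for quality of life: difference 12.3, SD 17.6, two-sided alpha 0.05, power 0.80.

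n = 2 × (1.96 + 0.84)² × 17.6² / 12.3² = 32.1, rounded up to 33 per group.

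This matches the stated 33 (power by the exact t-test at 33 is 0.798). For dropout, 33 / 0.80 = 41.25, against the stated 41. No figure is given for any blood count, so nothing below changes 33, 41 or 82.

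**2. The passages side by side.**
- Hypothesis (Background): hematological indicators improve more with exercise.
- Outcome list: indicators are included, transfusion is not.
- Definition: measured peripheral counts, with no transfusion rule.
- Table 1: transfusion number and volume, at t3 only.
- Analysis: t-test, ANOVA and repeated measures, taking account of age, gender and education level only.

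The Table 1 row connects to none of the others.

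**3. Direction of the effect.** Suppose a fraction p_C of controls and p_T of the exercise arm have a value raised by r through transfusion. Then

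observed difference = true difference − r × (p_C − p_T).

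With the same trigger in both arms, the arm with poorer recovery has the larger p. The subtracted term then has the sign of the true difference and works against it.

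**4. Illustration of size.** Every hematological input here is assumed; none is in the document, and the thresholds are not proposals for practice. Control HB has mean 85 and SD 15 g/L, values are normal, and there are 33 per group. The true difference is 10.5 g/L, the same standardised effect as the plan's quality-of-life assumption (15 × 12.3 / 17.6 = 10.5), so power is 0.80 without transfusion. A patient below the threshold is transfused and the value rises by r. Fractions come from the normal distribution. For example, at threshold 80, p_C = Φ((80 − 85)/15) = 0.369 and p_T = Φ((80 − 95.5)/15) = 0.151. Power comes from simulation with 20,000 runs per scenario.

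| Threshold, both arms (g/L) | p_C − p_T | Observed difference, r = 10 / 20 / 30 | Power, r = 10 / 20 / 30 |
|---|---|---|---|
| 60 | 0.039 | 10.1 / 9.7 / 9.3 | 0.80 / 0.79 / 0.76 |
| 70 | 0.114 | 9.4 / 8.2 / 7.1 | 0.79 / 0.74 / 0.63 |
| 80 | 0.219 | 8.3 / 6.1 / 3.9 | 0.77 / 0.64 / 0.31 |

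Worked entry: 10.5 − 30 × 0.219 = 3.9 g/L.

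**5. Can the sign reverse?** With a common threshold of 80, a change of sign would need r above 10.5 / 0.219 = 48 g/L, outside the range tried. With controls transfused below 80 and the exercise arm below 70, p_C − p_T = 0.369 − 0.045 = 0.325. The observed difference is then 7.3, 4.0, 0.7 and −2.5 g/L for r = 10, 20, 30 and 40. Reversal appeared only in the last of these.

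**6. False positives.** With no true effect and a common threshold of 70 (r = 20), the rejection rate stayed at 0.05. With unequal thresholds (80 and 70, r = 20), the difference was −4.2 g/L and the rejection rate 0.36.

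**The case against.** The strongest reply is that the article is silent rather than wrong. Rules for recently transfused values, and the choice of scale for a secondary laboratory outcome, commonly belong in an analysis plan, which is not shown. Table 1 also lists recruitment and drop-out rates that are not named as outcomes, so an unused row proves little. This stands in part: an unseen plan may use the transfusion data. However, the article itself fixes the outcome list, the definition, the tests and the adjustment variables, and that stated comparison is the one open to attenuation. The mismatch with Table 1 is visible in this document.

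A second reply is that follow-up starts only at engraftment, about day 14, and that T1 and T2 are discharge milestones, so transfusions may be few. That is possible, and the threshold-60 row shows that the loss is then negligible.

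Some readers might go further than the document allows:
- **Transfusion could reverse the result or create a false one.** In the scenarios run, this needed transfusion practice to differ between arms. The document does not show that. Those delivering the intervention are unblinded, but nothing says that they order transfusions.
- **The plan expects skewed counts and still relies on means.** The text is conditional and switches the summary to medians if data are non-normal. What remains is that no rank-based or transformed comparison is named for that case.
- **All four indicators are affected.** Red-cell and platelet transfusions do not directly raise neutrophils, and do not raise reticulocytes in the same way.

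**Conclusion.** The concern holds as a risk of attenuation in two secondary measures, HB and PLT, together with a listed assessment that has no stated purpose. It rests on two premises: transfusion goes to patients with low values and raises those values, and some transfusions occur close enough before T1, T2 or T3 to affect the measured count. The size is unknown. Under the assumptions shown, the loss ranges from trivial (10.5 observed as 10.1 g/L, power about 0.80) to serious (3.9 g/L, power 0.31), and the document gives no basis for choosing within that range. The point is minor: it bears on how hypothesis 3 is read, and the improvement is cheap.

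**What to change.** 1. Name the number and volume of red-cell and platelet transfusions from T0 to T3 as a secondary outcome, and compare them between arms. Read the HB and PLT results alongside this comparison.
2. Do not enter transfusion as a covariate in the HB or PLT models. It follows randomisation and may itself be affected by the intervention.
3. Compare the counts with the T0 value as covariate, on a log scale or by a rank-based method if they are skewed. The text says that all outcomes are measured at T0, but Table 1 has no mark for the indicators at t0, so the table should be brought into line.
4. Where transfusion dates can be obtained, add a sensitivity analysis for HB and PLT values measured shortly after a transfusion, with the window and the handling fixed in advance. A single total at t3 cannot show whether a T1 or T2 value followed a transfusion, so this step needs dates.

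Items 1 to 3 cost wording and a few extra analyses, using data already listed for collection. Item 4 costs the date extraction; the document does not name the source of the transfusion data, so the effort should be checked first. Transfusion practice is not changed by any of this.

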#### Adherence

In addition, an exercise rehabilitation log was issued to the participants during the exercise period. The exercise log, which was required to be recorded faithfully each day, covered several aspects including type and duration of exercises, subjective exercise responses (like the assessment of pain, fatigue, emotional state, and distress), and adverse events. When no exercise was performed, the reason should be provided. The first two phases of exercise rehabilitation were supervised by the interventionists, while the third phase of out-of-hospital exercise rehabilitation was supervised by daily WeChat exercise punch cards and weekly telephone contact. The exercise rehabilitation program was from the participant’s neutrophil and platelet engraftment after transplantation (approximately 14 days post-transplantation) to 100 days post-transplantation.

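### LOCF has no exception for exercise adherence, so an in-hospital attainment status can be carried into the home phase and the T3 rate may be overstated

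*Protocol article*

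**What the plan says.** Primary and secondary outcomes lists exercise adherence as a secondary outcome, and the participant timeline (Table 1) schedules it at t1, t2 and t3. A T2 value therefore normally exists that could be carried to T3.

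Variables and measurement instruments defines the outcome: "it was assessed by the exercise attainment rate, which was the number of people attaining the standard/total number of people". The standard is: "Exercise attainment was defined as exercising at least thrice a week for 30 min or longer", with shorter bouts allowed if they add up. The section does not say whether the total means those allocated, those still followed, or those returning records.

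The Adherence section gives the data source: "The exercise log, which was required to be recorded faithfully each day". It also asks for explanations of gaps: "When no exercise was performed, the reason should be provided". The setting then changes at discharge. For the hospital stay, "The first two phases of exercise rehabilitation were supervised by the interventionists"; the home phase is "supervised by daily WeChat exercise punch cards and weekly telephone contact".

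Statistical analysis states one missing-data rule for everything: "Missing data were filled in using the Last observation carried forward (LOCF) and statistical analysis was conducted following the intention-to-treat (ITT) principle". The same section names exercise adherence among the variables to be summarised, as frequencies and percentages.

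**The concern.** For a questionnaire score, a missing value is a gap in knowledge. For a behavioural outcome, a run of blank records may be the very event that the outcome should detect. LOCF fills that gap with the last known status. Here that status comes from T2, when staff supervised the exercise in hospital, and it would be reported as adherence at home.

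The home phase, from discharge to day 100, is where adherence is least certain. If its rate is inflated, a null quality-of-life result would be harder to interpret. It could be read as failure of a programme that patients followed, when some of them had stopped. Missing records are foreseeable: Limitations says that attrition by day 100 may be high, and Sample size allows 20% for losses.

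**Working it through.** **Arm size.** The protocol gives no expected adherence rate, so there is no adherence figure to reproduce. The arm size used below comes from the sample size calculation, which does reproduce. With a difference of 12.3, SD 17.6, two-sided alpha 0.05 and power 0.80:

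n = 2 × (1.960 + 0.842)² × (17.6 / 12.3)² = 2 × 7.851 × 2.047 = 32.1, rounded up to 33 per group.

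33 / 0.80 = 41.25; the protocol states 41.

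**What happens to a silent patient.** Take a patient in the exercise arm with no log, no punch card and no information from the weekly call after T2.

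- Intention-to-treat keeps the patient in the denominator.
- LOCF then sets the numerator: attained at T2 counts as attained at T3, and not attained at T2 counts as not attained at T3.
- If the total is instead read as those with records, the patient leaves both numerator and denominator.

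**Formulas.** Let N = 41, m = number silent at T3, p = share attaining among the N − m with records, and q = share of the silent who attained at T2.

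- A, silence scored as not attained: p(N − m) / N
- B, silent dropped: p
- C, LOCF: [p(N − m) + qm] / N

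If the silent did stop, A is the true rate. The excess is then pm/N under B and qm/N under C.

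**Main case (p and q are assumptions).** m = 8 is 8/41 = 19.5%, close to the 20% allowance; p = 0.70.

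- A: 0.70 × 33 / 41 = 23.1 / 41 = 56.3%
- B: 70.0%, an excess of 13.7 points
- C with q = 0.5: (23.1 + 4.0) / 41 = 66.1%, an excess of 9.8 points
- C with q = 0.7: (23.1 + 5.6) / 41 = 70.0%, an excess of 13.7 points
- C with q = 0.9: (23.1 + 7.2) / 41 = 73.9%, an excess of 17.6 points

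**Range over the number silent, p = 0.70.**

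| Silent (m) | A | B | C, q = 0.5 | C, q = 0.9 |
|---|---|---|---|---|
| 4 | 63.2% | 70.0% | 68.0% | 72.0% |
| 8 | 56.3% | 70.0% | 66.1% | 73.9% |
| 12 | 49.5% | 70.0% | 64.1% | 75.9% |

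With p = 0.50 and m = 8 the pattern is the same: A is 16.5 / 41 = 40.2%, B is 50.0%, and C runs from 50.0% (q = 0.5) to 57.8% (q = 0.9).

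The LOCF excess is zero when q = 0, and it does not arise for patients whose stopping is documented.

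**The case against.** The strongest reply is that the document does not force the error. Four parts of it stand.

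- A reader might infer that patients who stop are never counted as non-attaining. That is not so: a patient not attaining at T2 stays non-attaining under LOCF. In-hospital status is not automatically attained either. The Intervention section schedules aerobic sessions twice a week for 20 to 25 minutes and resistance sessions three times a week for 15 to 20 minutes, and does not recommend resistance work at the lowest platelet counts.
- A reader might call the home phase unsupervised. It is supervised remotely. The weekly call can establish that a patient has stopped, and patients still enrolled are seen again at T3. Where stopping is known, nothing is missing and LOCF does not apply.
- A reader might conclude that the T3 rate is overstated as a matter of fact. The total can also be read, under intention-to-treat, as everyone allocated, with a week without punch cards simply failing the standard. On that reading there is no inflation. That silent patients have stopped is plausible, but it is an assumption.
- A reader might tie the protocol's claims of feasibility and wide use to this rate. The Discussion only states an expectation of acceptability and feasibility, and the Conclusions make wide use conditional on effectiveness. Neither rests on the adherence figure.

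It can also be said that denominators and diary scoring belong in a full protocol or analysis plan that is not shown. That is fair for the denominator taken alone. It does not answer the LOCF part, because there the article states a rule, applies it without exception, and the rule suits this outcome badly. Nor does the separately listed drop-out rate repair it: showing losses beside an inflated rate does not correct the rate.

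**Conclusion.** The point holds in conditional form. As written, LOCF can turn a T2 status earned under in-hospital supervision into a home-phase result for patients who then go silent and cannot be reached, so T3 adherence may be overstated. Dropping such patients from the total has the same effect.

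The size cannot be fixed from the document. With 8 of 41 silent and 70% of the rest attaining, the overstatement would be about 10 to 18 points under LOCF (50% to 90% of the silent attaining at T2) and about 14 points if the silent are dropped. This rests on assumed attainment rates and on the silent having stopped.

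Adherence is a descriptive secondary outcome. The primary quality-of-life comparison and the sample size are not affected.

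**What to change.** In Statistical analysis, exempt exercise adherence from LOCF.

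In Variables and measurement instruments:

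- set the denominator as all participants allocated to exercise and alive at the start of the phase;
- score a week with no log, punch card or call confirmation as not attained;
- report phase 3 separately from phases 1 and 2;
- use the reasons for non-exercise, already collected under Adherence, to show medically required pauses apart from patient-chosen stopping.

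The cost is a few sentences and no new data. The reported rate will be lower, and some patients who exercised without reporting will count as non-attaining unless the weekly call corrects this.
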